### 4.4. Data and Statistical Analysis

Data forms and questionnaires will be coded in a standardized format and entered into our database. Digital measures/recordings will be similarly tracked in our database and regularly backed up. Analyses will be conducted using standard statistical software such as STATA version 18.5 and R version 4.4.2.

The primary outcome will be a change in the UPDRS total score from the baseline. Secondary outcomes include change scales that measure improvements in UPDRS subdomains, motor and cognitive function, mood symptoms, sleep disorder, fatigue, voice quality, olfactory and gustatory disorder, freezing of gait episodes, and QOL comparing pre- and post-TPS. These results will be used to determine the best effect of TPS intervention for a more extensive study in patients with PD. Differences between the two groups (pre- and post-TPS) will be tested using a paired Student’s *t*-test, and, in addition, we will also test the time effect in general mixed regression models adjusting for age, gender, and PD severity. This model will be used for the primary and secondary outcomes. Secondary analyses will be conducted as exploratory, and for this reason, we will not apply formal correction for multiple comparisons. Since this is a pilot study with a small sample size, our aim is to identify possible trends and generate hypotheses for future confirmatory trials. Accordingly, all results from secondary analyses will be interpreted with caution. A similar analysis will be conducted for the adverse effects. We will also use the uncorrected *p*-value for safety analysis to increase the likelihood of detecting harmful adverse effects.

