### 4.3. Safety

Adverse effects (AEs) questionnaires will be applied after every intervention session, allowing participants to grade the severity (mild, moderate, or severe) and indicate the perceived relationship to the intervention (none, remote, possible, probable, or related). In addition, a 20-min resting-state EEG will be conducted to monitor brain activity and investigate potential epileptiform discharges at baseline, after the first session, and after every three sessions (weekly), including a follow-up. Although not intended as a sole safety measure, EEG data will complement our clinical monitoring. Safety will also be assessed through clinical outcome scales (UPDRS, NMSS, and SPMSQ), where the absence of significant deterioration between baseline and post-intervention will support safety conclusions.

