## 5. Expected Results

The proposed study aims to evaluate the safety and efficacy of TPS in addressing both motor and non-motor symptoms of PD, utilizing a sophisticated neuronavigational system to personalize the intervention based on individual patient symptoms and requirements. Despite the inherent limitations associated with this pilot open-label trial—such as a small sample size, absence of a control group, and potential placebo effects—this research can generate critical preliminary data to inform future randomized, double-blinded, controlled studies. We expect to observe significant improvements in motor and non-motor symptoms after 12 sessions of TPS, with remaining effects after a 1-month follow-up. Additionally, the reason for assessing subjects after every three intervention sessions is that we might observe improvements in symptoms such as tremor and loss of smell and taste in less than 12 TPS sessions. Moreover, as TPS, a non-invasive neuromodulation method, is known for its minor side effects, typically limited to mild local discomfort or pressure, we do not expect to observe severe adverse events, proving that TPS is a safe technique for this population.

This study protocol distinguishes itself from other neuromodulation studies through TPS’s capability for individualized, precise, focused brain stimulation that is trackable in real time throughout the intervention. Furthermore, TPS allows pulses to be strategically directed to different brain regions and specific target areas of interest. An additional strength of this protocol is its structured assessment schedule after every three intervention sessions, allowing investigators to evaluate the minimal number of sessions required to achieve significant improvements in patients with PD. It is important to highlight that the TPS equipment can deliver sham stimulation, which maintains the same features as active stimulation but is indistinguishable from active stimulation and replicates all operational aspects such as machine sounds and procedural setup, thereby facilitating blinded controlled trials in the future. In the long term, if TPS proves its safety and efficacy in the PD population, this non-invasive neuromodulation technique can be applied in clinical practice as a targeted-individualized treatment to improve the quality of life for patients living with PD.

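### The analysis stated for the adverse-effect questionnaire does not fit post-session data with no stated pre-TPS value, and no severe event in 14 patients would not prove safety

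*Protocol article*

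**What the plan says.** Section 4.4 (Data and Statistical Analysis) gives two methods for the outcomes. The first is a paired test: "Differences between the two groups (pre- and post-TPS) will be tested using a paired Student’s" t-test. The second is a model: "we will also test the time effect in general mixed regression models adjusting for age, gender, and PD severity". It then adds: "A similar analysis will be conducted for the adverse effects". The next sentence leaves safety p-values unadjusted so that harm is more likely to be picked up.

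Section 4.3 (Safety) describes the data. On timing it says: "Adverse effects (AEs) questionnaires will be applied after every intervention session". On content, the form is described as "allowing participants to grade the severity (mild, moderate, or severe) and indicate the perceived relationship to the intervention", with five levels for relationship. The same section schedules EEG "at baseline, after the first session, and after every three sessions (weekly), including a follow-up". It also uses UPDRS, NMSS and SPMSQ as safety measures, "where the absence of significant deterioration between baseline and post-intervention will support safety conclusions".

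Section 5 (Expected Results) states the anticipated conclusion: "we do not expect to observe severe adverse events, proving that TPS is a safe technique for this population".

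**The concern.** Safety is a headline aim of the study (Abstract, sections 1.2 and 2), and the AE questionnaire is its most direct safety instrument. Two things look wrong.

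- **Test and data do not match.** A paired pre/post test needs a value from before treatment, and none is stated for this questionnaire. The relationship rating cannot have one, because there is no intervention to relate to before the first session. The other method, a time effect, asks whether AEs rise or fall as sessions accumulate. It does not ask how often they occur. A p-value from it cannot do the job section 4.4 gives it, which is to detect harm.
- **The conclusion outruns the sample.** Finding no severe event in 14 patients in a single arm is weak evidence about the risk of such an event. Section 5 nevertheless calls it proof, and later in the section links proven safety and efficacy to use in clinical practice.

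If the plan were followed as written, the main AE data could be summarised by a non-significant time effect and a count of zero severe events. Both could be read as evidence of safety when neither measures the risk.

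**Working it through.** **Step 1. Does each stated method apply to each safety measure?**

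| Safety measure | Timing (section 4.3) | Paired pre/post test | Time-effect model |
|---|---|---|---|
| AE questionnaire | after each of 12 sessions; no pre-TPS value stated | no stated pre value | can be fitted; tests trend over sessions only |
| EEG | baseline, after session 1, weekly, follow-up | baseline available | baseline available |
| UPDRS, NMSS, SPMSQ | baseline against post-intervention | baseline available | baseline available |

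The mismatch affects the first row only. The AE items there are also ordinal (three severity grades, five relationship grades), which a t-test on means does not suit.

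**Step 2. What would the time effect show for AEs?** Let p_s be the probability that a patient reports a given AE after session s. The time effect tests whether p_1 = p_2 = ... = p_12. As an illustration, take fatigue at the 50% per-patient frequency that section 1.1 reports from an observational TPS study in PD. Suppose that the same half of the patients (0.50 x 14 = 7) report it after every session. Then p_s = 0.50 throughout, the change from session 1 to session 12 is 0.50 - 0.50 = 0, and there is no time effect to detect. The same would hold at any constant rate. The model's intercept would carry the level, but section 4.4 says that it is the time effect that will be tested. The constant pattern is my assumption and serves only to show what the test cannot see.

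**Step 3. What can zero severe events in 14 patients show?** The document gives no precision figure for safety, so there is none to reproduce. The sample size of 14 in section 4.5 was set for the primary efficacy test. Inputs: n = 14 (sections 2 and 4.5) and x = 0 severe events (the expectation in section 5).

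Exact binomial upper limit for x = 0: 1 - a^(1/n).

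- Upper end of the two-sided 95% interval: 1 - 0.025^(1/14) = 0.232, or 23.2%.
- One-sided 95% limit: 1 - 0.05^(1/14) = 0.193, or 19.3%.

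Chance of seeing no event in 14 patients when the true per-patient risk is p: (1 - p)^14.

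| True risk p | Calculation | Chance of no event |
|---|---|---|
| 2% | 0.98^14 | 75% |
| 5% | 0.95^14 | 49% |
| 10% | 0.90^14 | 23% |
| 20% | 0.80^14 | 4.4% |

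A severe AE affecting 1 patient in 20 would go unseen in about half of all trials of this size. One affecting 1 in 10 would go unseen in nearly a quarter.

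**The case against.** The strongest reply is that section 4.4 promises a similar analysis, not the same one. It sits among remarks about exploratory status and caution, and one of its two methods, the mixed model, can be run on 12 post-session questionnaires per patient. That is right, and a reader who inferred that no AE analysis could be computed would be going too far. Loose wording does not fully rescue the plan, however. The sentence on unadjusted safety p-values shows that a hypothesis test is meant, and the test that can be run does not address occurrence.

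A reader might also infer that the safety plan as a whole lacks baselines. It does not: EEG and the clinical scales have them. Nor does section 4.3 rule out a baseline symptom check. It simply states none, and the study scheme in Figure 1 is not visible in the text reviewed.

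A further tempting inference is that AE counts cannot be interpreted at all without a baseline checklist. The documents do not support this. Section 1.2 lists fatigue among the PD domains, but section 4.2 lists PFS-16, which Table 1 scores at baseline for targeting. Nothing in the documents says that headache or dizziness is common in PD without TPS, and each AE carries a relatedness rating.

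On section 5, it is fair to say that the sentence is expectation, not a decision rule, that the same paragraph names the small sample and missing control group, and that the section ends conditionally. Those caveats are general and do not qualify the safety statement, which comes after them in the same paragraph. An article may also leave detailed AE tables to a full protocol or analysis plan. Their absence is not the point here. The point is that the analysis and the conclusion the article does state do not fit.

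**Conclusion.** The point holds for the AE questionnaire and for the safety sentence in section 5. For the questionnaire, the paired test has no stated pre-TPS value, and the mixed model yields a trend over sessions that would miss AEs at a constant rate. For the conclusion, 0 of 14 leaves a per-patient risk of up to 23.2% (two-sided) or 19.3% (one-sided) unexcluded, and a 5% risk would yield no event 49% of the time.

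The figures assume that all 14 patients are treated, that patients are independent with a common risk over the course, and that no severe event is seen. Any patient treated at least once contributes questionnaire data, so treated patients are the right denominator. A limit based on a smaller number of completers would need a dropout figure that the documents do not give. The baselines for EEG and the clinical scales are not in question, and the AE data as collected are adequate for descriptive reporting.

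**What to change.** 1. **Section 4.4.** For the AE questionnaire, replace the sentence on a similar analysis with: the number and proportion of treated patients with at least one AE, by type, severity and relatedness, each with an exact 95% confidence interval, and an AE rate per session with the patient as the cluster. If a time-effect model is kept, describe it as a test of trend over sessions only.
2. **Section 5.** Replace the claim of proof with a statement such as: if no severe AE occurs in 14 patients, a true per-patient risk of up to about 23% is not excluded.
3. **Optional.** Give the symptom and severity items of the questionnaire, without the relatedness item, once at the existing baseline visit, so that symptoms already present before TPS can be recognised.

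Items 1 and 2 change wording only and make the safety claim more modest. Item 3 costs one short questionnaire. None adds a visit or a patient.

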Although it is a novel technology, TPS has shown many positive effects in other neurological disorders, such as mild neurocognitive disorders [29,30], Alzheimer’s disease (AD) [31,32,33,34,35,36,37,38], disorders of consciousness [39], autism spectrum disorder [40,41], attention deficit hyperactivity disorder [42,43], and depression [36,44]. In most of these studies, TPS has shown considerable potential in reducing depressive symptoms and enhancing different aspects of cognitive performance. A recent observational study reported that 10 sessions of TPS therapy were safe in PD subjects and led to improvements in clinical motor function in optimized PD patients with only mild and transient side effects (fatigue [50%], headache [30%], and dizziness [30%], which resolved within one day) [45]. Their findings showed a significant reduction in the Unified Parkinson’s Disease Rating Scale part III (UPDRS-III pre-TPS: 16.70 ± 8.85, UPDRS-III post-TPS: 12.95 ± 8.55; *p* < 0.001; Cohen’s d = 1.38), and none of the participants experienced worsening of their motor status. However, this study has some limitations, primarily related to its retrospective design, small sample size, lack of a sham control group, and the heterogeneity of the study population and protocol. A study showed positive effects on the motor functions of PD patients after even a single treatment with TPS of the motor cortex M1 in comparison to a sham group [46].

Findings from AD studies suggest that TPS might induce improvements in cognitive impairment and depression symptoms, with potential application in PD for both motor and non-motor symptoms [29,44]. Fong et al. (2023) [29] observed improved cognitive function in 19 elderly participants with mild neurocognitive disorder after six TPS open-label sessions. Results showed increasing MoCA scores: pre-TPS: (19.32 ± 4.52), post-TPS (21.16 ± 3.98), and 12-week follow-up (20.58 ± 4.29), with a one-way ANOVA effects of time of F (3, 54) = 4.99, *p* = 0.004. Moreover, Cheung et al. (2023) [44] in a pilot randomized controlled trial demonstrated a reduction in depression symptoms in the TPS group (mean difference = −6.60, *p* = 0.02) in comparison to the control group in a study with 30 subjects who underwent six sessions of TPS.

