## 2. Experimental Design

This is an open-label, single-arm pilot study (NCT06676995) designed to assess the safety and feasibility of TPS for improving overall PD symptoms, with a total sample size of 14 subjects to be conducted at Spaulding Rehabilitation Hospital, Cambridge, USA. This study consists of a consent and enrollment visit, a magnetic resonance imaging (MRI) brain scan, 12 sessions of TPS (3 sessions per week), and 6 assessment sessions—a baseline visit, after every 3 TPS sessions, and a 1-month follow-up visit after the last TPS session. Also, 1 assessment visit will be performed after every 3 TPS sessions. See the study scheme provided in Figure 1. Participants will primarily be recruited through extensive methods such as advertisements online and in local newspapers. The inclusion criteria are as follows: (i) age between 40 and 90 years old; (ii) diagnosis of “probable” or “possible” PD, as defined by the current clinical criteria [47] or as confirmed by a co-investigator neurologist or confirmation via medical records or a letter from a patient’s physician; (iii) disease stages 2 to 4 based on the UPDRS subdomain V (or Hoehn and Yahr scale); (iv) taking a stable regimen of anti-parkinsonian medications, defined as no changes in drug type, dosage, or administration frequency, for at least 30 days before study entry.

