## 4. Detailed Procedure

### 4.1. Intervention

The TPS session sequence will be (1) individual, (2) standard (homogeneously across all brain areas), and (3) foot sole. As previously noted, up to four specific and personalized brain regions of interest will be targeted for individual intervention. For all patients, one of these four areas will be the entire strip of the primary motor cortex (1000 pulses), and the other 3000 pulses will be chosen according to the patient’s three most important clinical features.

During treatment, a camera system will monitor the positions of both the handpiece and the patient’s head using goggles equipped with infrared markers. This individual real-time tracking system allows for standardized focal brain stimulation across the entire study population, ensuring proper movement of the handpiece over the skull, as displayed in Figure 2. Furthermore, it will enable the tracking of the stimulation pulses, with each pulse leaving a colored mark in the visualization. The TPS intervention will use an energy flux density of 0.25 mJ/mm^2^ at a focus depth of 5 cm, with the useful energy dispersed between 2 and 8 cm. The frequency of application (pulse repetition rate) will be set at 4 Hz, with a coupling medium of water-based gel applied to the scalp.

During TPS, a generous amount of bubble-free ultrasound gel is applied sequentially to the skin and hair in the treatment area to prevent any acoustic impedance barriers. TPS application will be conducted in a continuous sweeping motion, lasting approximately 40 to 45 min per session, resulting in a total applied energy of 50 Joules (5 mJ/pulse with 0.25 mJ/mm^2^). The handpiece will be kept perpendicular to the skull for highly focused applications throughout the treatment. The entire treatment session will then be recorded for subsequent evaluation of the precise localization of individual intracerebral pulses, as presented in Figure 3.

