### 4.5. Sample Size and Power Calculation

To determine the sample size for this study, we considered the change in patients’ overall symptoms measured via the UPDRS from baseline as the primary outcome for our statistical analysis. Based on our pilot study of the effects of TPS in another neurodegenerative condition, we used the smallest effect size of d = 1.5 [31]. We calculated a minimum sample size of 14 participants for a within-group two-tailed paired *t*-test. Although a sample size of 14 subjects is relatively small, it can still provide valuable preliminary data and insights into the feasibility and potential efficacy of the intervention. This pilot study focuses on exploring trends, feasibility, and potential effect sizes rather than achieving statistical significance. However, a sample size of 14 subjects would provide a power of at least 80% (alpha = 0.05) to detect a mean difference of greater than 30% in overall symptom improvement between the pre- and post-stimulation, which is also what our AD study has shown [31]. This AD pilot study with only 10 patients could demonstrate a significant reduction in neuropsychiatric symptoms with large effect sizes (d = 1.5 and d = 2.3). Note, data from trials using MDS-UPDRS when investigating other NIBS therapies (tDCS and TMS) in PD patients was used to estimate the variances for this power analysis, which showed around 20% standard deviation and an effect size of about d = 1.29, even though the studies analyzed other NIBS rather than TPS [67,68]. Although it could interfere with the study power, we do not account for potential dropouts to calculate our sample size due to the preliminary analysis and small sample size. For this reason, the results from our pilot study will inform the design of future larger-scale studies and contribute to developing hypotheses for further investigation.

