**Figure 3 bioengineering-12-00773-f003:**
[figure not shown]
Examples of the TPS intervention strategy based on baseline assessments: (**a**) UPDRS-III score > 33 and a BDI score ≥ 14, pulse distribution: 1000 on M1 (each hemisphere), 1000 DLPFC (each hemisphere), and 4000 distributed across the brain areas (as standard intervention); (**b**) UPDRS-III score > 33 and VHI-10 ≥ 11, pulse distribution: 1000 on M1 (each hemisphere) and 1000 inferior frontal cortex extending on the left to Broca’s area (each hemisphere); (**c**) SCOPA-COG ≤ 24 and VHI-10 ≥ 11, pulse distribution: 500 on M1 (each hemisphere), 750 DLPFC (each hemisphere), and 750 inferior frontal cortex extending on the left to Broca’s area (each hemisphere); (**d**) PFS-16 binary score of >8, PDSS-2 score ≥ 18, 500 on M1 (each hemisphere), 750 DLPFC (each hemisphere), and 750 PPC. Additionally, 4000 will be distributed across the brain areas as a standard intervention. Horizontal and vertical lines reflect the position of the Coronal, Sagittal and Axial planes. Circular and oval shapes mark the areas of interest for the intervention.

**Table 1 bioengineering-12-00773-t001:** Representation of the patients’ symptoms and target brain regions of interest for TPS individualized intervention.

Symptoms	Clinical Feature	Test Definition	Brain Region of Interest
Motor impairment	Moderate to severe rigidity, freezing of gait, postural instability, tremor, and bradykinesia	UPDRS-III score > 33	Bilateral and entire strip of the primary motor cortex (M1)
Cognitive impairment	Mild memory and executive function alterations	SCOPA-COG ≤ 24	Bilateral dorsolateral prefrontal cortex (DLPFC)
Psychiatric disorder	Depression	BDI-II score ≥ 14	Bilateral dorsolateral prefrontal cortex (DLPFC)
Sleep disorder	Moderate to severe sleep disturbance	PDSS-2 score ≥ 18	Bilateral posterior parietal cortex (PPC)
Fatigue	Moderate to severe fatigue	PFS-16 binary score of >8	Bilateral dorsolateral prefrontal cortex (DLPFC)
Voice/speech dysfunction	Moderate to severe dysarthria and poor voice control	VHI-10 score ≥ 11	Bilateral inferior frontal cortex extending on the left to Broca’s area
Taste and smell disorders	Moderate or severe olfactory and gustatory dysfunction	VAS for taste or smell ≥ 4	Bilateral orbitofrontal

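### The scale-based safety rule tests only the group mean, so worsening confined to a few patients, such as those given one focal target, can go unseen

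*Protocol article*

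**What the plan says.** Section 4.3 collects adverse effects by questionnaire after every session, graded for severity and relationship, and repeats a resting EEG to look for epileptiform discharges. It then adds a rule for UPDRS, NMSS and SPMSQ: "the absence of significant deterioration between baseline and post-intervention will support safety conclusions".

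Section 4.4 gives the method: a paired t-test of pre against post, and a mixed model for time adjusted for age, gender and PD severity. For safety it says "A similar analysis will be conducted for the adverse effects". Neither target nor pulse count is a model term.

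The treatment has a common part and a varying part. Under section 3.2 everyone receives 4000 pulses spread over the brain and 2000 on the foot soles. A further 4000 go to individual targets. Section 4.1 says of these: "one of these four areas will be the entire strip of the primary motor cortex (1000 pulses), and the other 3000 pulses will be chosen", by the patient's leading symptoms. Table 1 lists the regions, among them "Bilateral orbitofrontal".

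Section 5 expects no severe adverse events, "proving that TPS is a safe technique for this population".

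**The concern.** The scale rule draws a safety conclusion from a mean over 14 patients whose focal treatment is not the same. If the patients given extra pulses at one region deteriorate and the rest improve, the mean can improve and the rule is met. The article itself expects significant improvement on motor and non-motor symptoms, which is the condition under which a worsening minority is hidden.

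Safety is a main aim, and the results are meant to inform larger trials. The earlier observational PD study described in section 1.1 could report that "none of the participants experienced worsening of their motor status". A non-significant group change does not by itself yield a statement of that kind.

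**Working it through.** **1. How much the focal treatment varies.** Individual pulses from the four examples in the Figure 3 caption, both hemispheres added:

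| Region | (a) | (b) | (c) | (d) |
|---|---|---|---|---|
| DLPFC | 2 × 1000 = 2000 | 0 | 2 × 750 = 1500 | 2 × 750 = 1500 |
| Inferior frontal | 0 | 2 × 1000 = 2000 | 2 × 750 = 1500 | 0 |
| M1 | 2 × 1000 = 2000 | 2 × 1000 = 2000 | 2 × 500 = 1000 | 2 × 500 = 1000 |

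The M1 totals in (a) and (b) do not match the 1000 pulses that section 4.1 gives for every patient. The two places must be reconciled before pulse counts are tabulated.

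**2. The plan's own figure.** Section 4.5 gives a "minimum sample size of 14 participants for a within-group two-tailed paired" t-test, with at least 80% power. By the noncentral t distribution, 14 patients have 99.9% power at d = 1.5 and 99.4% at d = 1.29, so the power statement is true. Fourteen is not the minimum at d = 1.5, where 6 suffice for 80%; that is a separate matter. These powers assume an effect shared by all. Likewise, a harm of 1 SD shared by all 14 would be detected about 93% of the time.

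**3. Harm confined to 3 of 14.** The article gives neither the number per target nor a harm size, so both are assumptions here. Change is in units of its SD, positive for worsening; d = 1.29 is read on the same scale. Three patients have mean +1 and the other 11 have mean *m*. The expected group mean is (3 × 1 + 11 × *m*)/14. The test is a two-sided 5% paired t-test; the percentages come from simulation of at least 100,000 trials.

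| Other 11 patients | Expected group mean | Significant deterioration | Significant improvement |
|---|---|---|---|
| unchanged | 3/14 = +0.21 | about 8.5% | about 0.2% |
| improve by 0.5 SD | (3 − 5.5)/14 = −0.18 | about 0.2% | about 5% |
| improve by 1.29 SD | (3 − 14.19)/14 = −0.80 | about 0% | about 51% |

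The first row is low power: a larger trial with the same mix would find the shift. The other two are not. There the true mean lies on the side of improvement, so with the same mix a larger sample only makes significant improvement more likely.

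With the others unchanged and the number harmed varied, detection is about 6% for 2 harmed, 18% for 5 and 32% for 7.

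**4. What zero events would show.** The one-sided 95% upper bound on risk after no event in *n* patients is 1 − 0.05^(1/*n*).

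- *n* = 14: 19%
- *n* = 5: 45%
- *n* = 3: 63%
- *n* = 2: 78%

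The first applies to the whole sample ("with a total sample size of 14 subjects"). The others apply to a target boosted in that assumed number of patients.

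**The case against.** The strongest reply is that the trial asks whether personalised TPS, as a strategy, is safe and feasible, and pooling everyone who received it answers that. This stands, and the pooled analysis should stay.

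A reader might infer more than the article supports, in four ways:

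- **That all harm is averaged away.** It is not. Adverse effects and EEG are recorded per patient, and section 4.1 records each session so that pulses can be localised. An event in one patient stays visible and can be tied to the targets received.
- **That some regions go unstimulated.** Every patient receives the 4000 homogeneous pulses and M1 targeting. Only the extra focal dose may reach few or none. The absence of an orbitofrontal case from Figure 3 says nothing about enrolment, since the figure shows examples only.
- **That the article claims safety region by region.** It does not. The statement in section 5 is general, concerns expected severe events, and stands beside an admission of the small sample and missing control group.
- **That the rule prevents a count of patients who worsened.** Individual scores are collected, so the count can be made. The stated rule simply does not use it.

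Two further objections hold. Tables by target are commonly left to a full protocol or SAP, so their absence is no fault. And analysis by target could not isolate target-specific harm: targets overlap within patients and follow symptoms, so region is confounded with disease profile.

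What the objection does not remove is the criterion itself. The article states the scales, the test, the covariates and the inference drawn from non-significance.

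**Conclusion.** The concern holds for the scale comparisons in sections 4.3 and 4.4 and for any paired test of adverse-effect scores. Met as written, the rule could support safety although several patients had worsened. Under the assumed 1 SD worsening in 3 of 14, the chance of a significant deterioration is about 8.5% at best and about 0% if the rest improve as the cited stimulation trials suggest. The exact percentages depend on those assumptions; that a mean can hide a worsening minority does not.

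The wording of proof in section 5 also outruns the data: no event in 14 patients would still allow a risk of up to about 19%. The point is a cheap improvement to a stated rule. It does not invalidate the pooled safety analysis.

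**What to change.** Keep the pooled analysis and make four changes.

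1. In sections 4.3 and 4.4, add a listing by participant of change on UPDRS, NMSS and SPMSQ, adverse effects and new EEG findings, beside the targets and pulse counts taken from the session recordings.
2. State how many participants worsened on each scale, with an exact 95% interval, and rest the safety statement on this as well as on the mean. Define worsening beforehand. For illustration, 3 of 14 gives a two-sided exact interval of about 5% to 51%.
3. Report how many participants received extra pulses at each target, as description only and without tests by target.
4. In section 5, replace the claim of proof with a preliminary statement about the personalised strategy in 14 patients, giving the upper bound on risk and making no claim for targets boosted in few or no patients.

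The cost is some wording and one or two descriptive tables from data already planned, with no new patients or visits. The price is a narrower safety claim.
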